#### Physical Fitness

Physical fitness includes a peak, symptom-limited CPET. The CPET will be performed on a treadmill T-2100 (General Electrics Healthcare, Germany) in the cardiology department of the Alava University Hospital. The testing protocol will start with 1.6 km/h with a 0% slope, with gradual increments of 0.1 km/h and a 1% slope every 15 s to exhaustion with continuous electrocardiogram monitoring. During the test, participants will be verbally encouraged by the nurse in charge of the test. The expired gas analysis will be conducted using a commercially available system (Ganshorn, Germany) that will be calibrated before each test with a standard gas of known concentration and volume. Breath-by-breath gas exchange data will be measured continuously during exercise and averaged every 60 s. Peak oxygen uptake is defined as the highest oxygen uptake (VO_2peak_) value attained toward the end of the test. Achievement of true peak effort can be assumed in the presence of two or more of the following criteria: (1) volitional fatigue (>18 on BORG scale), (2) peak respiratory exchange ratio (VCO2/VO2) ≥1.1, (3) achieving >85% of age-predicted maximum heart rate (HR), and (4) failure of VO_2_ and/or HR to increase with further increases in work rate (35). A self-reported Borg rating of perceived exertion (6–20 scale) will be recorded at the end of the test. Blood pressure will be measured every 2 min throughout the test. Ventilatory thresholds (i.e., VT1 and VT2) will be assessed by standardized methods using the V-slope and ventilatory equivalents. First ventilatory threshold (VT1) will be identified as the point of transition in the carbon dioxide production (VCO_2_) vs. VO_2_ slope from <1 to >1, or VT1 is identified as the nadir of the ventilatory equivalent (VE) of VO_2_ vs. work rate relationship. The second ventilatory threshold (VT2) is identifiable as the nadir of the VE/VCO_2_ vs. work rate relationship (35). Absolute and relative indications for terminating the exercise test will be taken into account (36). The identification of the two VT will determine the three different exercise intensity domains or ranges for exercise design (R1, R2, R3): (R1) light to moderate exercise intensity with HR values below VT1; (R2) moderate to high or vigorous exercise intensity with HR values between VT1 and VT2, and (R3) high to severe intensity exercise intensity with HR values up to VT2 to peak intensity. When it is not possible to identify the VT2, exercise intensity domains are established taking into account percentages of HR reserve, i.e., moderate intensity is defined between 50 and 75% of HR reserve, high intensity from ≥76% to <95% of HR reserve (35).

#### Clinical Variables

##### Diagnosis

Patients will be diagnosed according to the DSM-5 criteria using the semi-structured SCID-P interview (32).

Analysis of the pre-morbid adjustment of patients as part of a determination of their prognosis will be made using an *abbreviated version of the Phillips Scale of Pre-morbid Adjustment* (37). This scale is an abbreviated version of the original five-section Phillips Pre-morbid Rating Scale and is composed of two parts: Part I (Abbreviated Pre-morbid Sexual Rating Scale) and Part II (Abbreviated Pre-morbid Personal-Social Rating Scale). This scale uses a 7-point scale (0–6) to evaluate each part.

##### Psychosocial functioning

The functioning of patients will be measured using *the Functioning Assessment Short Test (FAST*) (38). This scale is a brief instrument designed to assess functional impairment in psychiatric disorders. The scale comprises 24 items that cover six specific areas of functioning: autonomy, occupational functioning, cognitive functioning, financial issues, interpersonal relationships, and leisure time. Each item is scored in a 0–3 points range (0: no difficulty; 1: mild difficulty; 2: moderate difficulty; 3: severe difficulty) with total score ranging from 0 to 72 points (39).

The patient functionality will be assessed through the *Global Assessment of* Functioning (GAF) (40). This scale rates the level of functioning and severity of symptoms on a 0–100 scale, with higher values corresponding to better overall functionality.

Strauss-Carpenter scale (41). This scale will be employed to assess the psychosocial functioning of patients and consists of four items rated from 0 to 4 on a Likert-type scale and yields a total score that is calculated by the addition of all item scores: the higher the score is, the better the prognosis (42).

##### Neurocognition

- *The Stroop Color and Word Test (SCWT)* (43): is a neuropsychological test that will be used to assess selective attention and the impulsivity domain, executive subject's ability to inhibit cognitive interference that occurs when the processing of a specific stimulus feature impedes the simultaneous processing of a second stimulus attribute, well-known as the Stroop Effect. Individuals are required to read three different tables as fast as possible. Two of them represent the neutral condition in which participants are required to read aloud a list of color name words printed in black ink and name different color patches. In contrast, in the third table, the conflict condition is provided by having color words written in an incongruous color of ink and participants are required to name the color of the ink instead of reading the word (44).- The Complutense Verbal Learning Test (TAVEC) (45): The TAVEC is the Spanish version of the California Verbal Learning Test (CVLT) (46) and will be used for the assessment of different memory and learning processes, such as immediate recall, short and long term memory with and without semantic clues and recognition (47).- The Computerized version of Wisconsin Card Sorting Test (WCST) (48): neuropsychological test that assesses individuals' executive function. WCST will be used to measure the subject's capacity to deduce concepts and apply a strategy to adapt behavior to changing conditions (49). This test consists of cards depicting simple geometric figures that vary in color, shape, and number. Examinees must sort cards in accordance with one of three viable rules: color, shape, or number of the depicted object(s) (50).

##### Clinical severity

- *The Clinical Global Impression Scale (CGI)* (51) will be used to assess symptom severity, global improvement and therapeutic response. This scale consists of two subscales that evaluate, respectively the clinical severity and the overall improvement in the patient's symptomatology. Each subscale has a single item scored between 0, not evaluated, and 7 which corresponds to the maximum severity (severity subscale) or to a state of no improvement and aggravated worsening of the symptomatology (improvement subscale).- The presence of suicidal thoughts or behaviors will be assessed by means of *the Likert Clinical Global Impressions–Severity of Suicide scale (CGI-SS)* (52). This scale scores from 1 to 5 the patient's current risk of suicide.

##### Illness awareness

The illness awareness of patients will be measured using *the Scale to assess Unawareness in Mental Disorders (SUMD)* (53). This scale explores the thoughts and beliefs of patients regarding their illness and its pharmacological treatment. SUMD scale comprises nine items (current awareness of the following states): (1) a mental disorder; (2) consequences of a mental disorder; (3) effects of drugs; (4) hallucinatory experiences; (5) delusional ideas; (6) disorganized thoughts; (7) blunted affective; (8) anhedonia, and (9) lack of sociability. Each item is scored as follows: not applicable (response of “0” or missing data), aware (response of “1”), slightly aware/unaware (response of “2”), and seriously unaware (response of “3”) (54).

##### Medication adherence

- Adherence to medication will be assessed using the *Morisky-Green scale*. This self-reported scale includes four yes/no questions rated on a 0–4 scale, considering patients who obtain 0 points as adherent and those who obtain a 1+ score as non-adherent (55).- Response to lithium will be measured by the *Retrospective Criteria of Long-Term Treatment Response in Research Subjects with Bipolar Disorder (Alda scale)* (56). This scale was specifically developed to evaluate the long-term mood stabilization effect under naturalistic conditions. Briefly, this scale quantifies the degree of improvement during the treatment (Criterion A), which is rated on a 0–10 scale, and weighs clinical factors that are considered to be relevant for determining if the observed improvement is a result of the treatment rather than a spontaneous improvement or an effect of additional medication (Criteria B1-B5), which are rated as 0, 1, or 2 points. The total score on the Alda scale is obtained by subtracting the B score from the A score (57).

##### Clinical symptomatology

- Depressive symptoms will be measured by *the Hamilton Rating Scale for Depression (HRSD*) (58). This scale consists of 17 items, each of which offers between 3 and 5 possible answers with values ranging from 0–2 or 0–4 points, respectively. The total score ranges from 0 to 52 points, and different cut-off points are used to classify the patient's depressive symptoms. Those who obtain scores of 0–7 are identified as non-depressed, minor depression 8–12, moderate depression 13–17, severe depression 18–29, and those who obtain scores above 30 are characterized as very severe depression (59).- Manic symptoms will be measured using *the Young Mania Rating Scale (YMRS)* (60). This scale is composed of 11 items, each item consisting of 5 answer choices that are scored on a 0–4 scale, except four of the 11 items that are scored with double points (0, 2, 4, or 8 points). The total score ranges from 0 to 60, with the status of euthymia being classified as getting 6 or fewer points, hypomania as getting 12 or more points, and mania as getting between 20 and 60 points.

##### Quality of lifestyle

- *The World Health Organization Quality of Life-BREF (WHOQOL-BREF) instruments* will be used to measure the quality of life. It assesses the individual's perceptions in the context of their culture and value systems, as well as their personal goals, standards, and concerns. The WHOQOL-BREF instruments comprise 26 items that measure the following broad domains: physical health, psychological health, social relationships, and environment (61).- The severity of substance addiction will be measured with the *European version of the Addiction Severity Index (EuropASI)*, a semi-structured interview, which measures the severity of addiction in different areas: medical, employment, alcohol consumption, use of other drugs, legal problems, family and social relationships, and psychological state (62).- Chronobiological rhythms will be assessed with the *Biological Rhythms Interview of Assessment in Neuropsychiatry (BRIAN)* (63). This scale contains 21 items designed to assess five domains related to biological rhythms: (1) Sleep, (2) Activities, (3) Social aspects, (4) Alimentation, based on the last 15 days, and (5) predominant Rhythm (chronotype) based on the last year. The total score may range from 16 to 84, with the higher the score obtained, the greater the alteration of the biological rhythms (64).

#### Biological Variables

Venous blood samples (10 mL) will be collected between 8:00 and 9:00 after overnight fasting by the nursing staff in polypropylene EDTA-containing tubes. Fresh blood will be stored at 4°C until processing about 1 h. later. Blood will be centrifuged (652 g × 10 min, 4°C); the resulting plasma samples will be collected and stored at −80°C until use. The rest of the sample will be diluted 1:1 in culture medium (RPMI 1640, GIBCO) and a gradient with Ficoll-Paque (GE Healthcare) will be used to isolate peripheral blood mononuclear cells (PBMC) by centrifugation [800 g × 40 min, room temperature (RT)]. The PBMC layer will be aspired and suspended in RPMI and centrifuged at 1800 g for 15 min, RT. The supernatant will be removed and the PBMCs pellet will be stored at −80°C until analysis.

##### Biochemical measurements in plasma

- *Nitrite (*${NO}_{2}^{-}$*):* The final and stable product of nitric oxide, will be measured in plasma using the Griess method (65). Briefly, in an acidic solution with 1% sulphanilamide and 0.1% N-(2-napthyl) ethylenediamine dihydrochloride (NEDA), nitrites will be converted into a pink compound that will be measured photometrically at 540 nm in a microplate reader (Synergy 2, BioTek).- *Lipid Peroxidation (TBARS):* In the process of lipid peroxidation, there are several intermediate and final products due to the degradation of cell membranes, among which is malondialdehyde (MDA), used as a marker of cellular damage. The Thiobarbituric Acid Reactive Substances (TBARS) test is the most used for the measurement of this metabolite in plasma where thiobarbituric acid (TBA) reacts with malondialdehyde (MDA) under high temperature (95°C) and acidic conditions to produce a MDA-TBA complex that is measured photometrically at 530 nm (Synergy 2, BioTek) (66). The results obtained through this procedure will be expressed in μM of MDA.- *Total Antioxidant Status (TAS):* This parameter reflects the cumulative effect of all antioxidants present in plasma and is determined by a standardized spectrophotometric assay. This assay is based on the ability of the antioxidants present in the sample to inhibit the oxidation of ABTS (2,2'-azino-bis-[3-ethylbenzothiazolin-6-sulfonic]) to the ABTS+ cation radical by the action of methemyoglobin (peroxidase). The concentration of this radical is measurable by spectrophotometry at 600 nm, the result of which is inversely proportional to the total antioxidant level of the sample (67).- *Prostaglandin Levels*: PGE2 plasma levels will be measured by a competitive colorimetric immunoassay in which the PGE2 present in the sample competes with the PGE2-linked conjugate (provided by the kit) for binding to the anti-PGE2 antibody present in the wells of the plate. Then the substrate is added which triggers a measurable enzymatic reaction at 412 nm (Synergy 2, BioTek). Since the concentration of the conjugated is constant, the intensity of the bound yellow color is inversely proportional to the concentration of PGE2 in the sample.- *Cytokine levels:* Plasma levels of IL-6 will be measured by enzyme immunoassays EIA kits, a technique based on recognition by specific antigen-antibody binding, both cytokines will be measured by spectrophotometry at 450nm in a microplate reader (Synergy 2, BioTek).- *Glutathione peroxidase (GPx)* catalyzes the reduction of hydroperoxides, including H_2_O_2_, by reduced glutathione and functions to protect the cell from oxidative damage. The measure of GPx activity is based on a coupled reaction with glutathione reductase (GR). Oxidized glutathione (GSSG) produced upon reduction of hydroperoxide by GPx is recycled to its reduced state by GR and NADPH. The oxidation of NADPH to NADP+ is accompanied by a decrease in absorbance at 340 nm. Under conditions in which the GPx activity is rate-limiting, the rate of decrease in the absorbance is directly proportional to the GPx activity in the sample.- *Glutathione (GSH)* serves as a nucleophilic co-substrate to glutathione transferases in the detoxification of xenobiotics and is an essential electron donor to GPx in the reduction of hydroperoxides. The oxidized GSH dimer (GSSG) is formed from GSH and H_2_O_2_ by the GPx. The detection of both forms, GSH and GSSG, could be detected using comercial kits, a colorimetric substance reacts with the free thiol group on GSH to yield a highly colored product that can be measured at 405 nm (Synergy 2, BioTek). On the other hand, by using 2-vinylpyridine to block any free GSH in the sample GSSG can be determined, because any sample that has not been treated with 2-vinylpyridine will yield Total GSH levels. Then, the free GSH concentration can be calculated from the difference between the total GSH and GSSG.- *BDNF levels:* An *in vitro* enzyme-linked immunosorbent assay will be used for the quantitative measurement of human BDNF in plasma. This assay employs an antibody specific for human BDNF coated on a 96-well plate. Standards and samples are pipetted into the wells and BDNF present in a sample is bound to the wells by the immobilized antibody. A secondary antibody HRP-conjugated is used for the detection of bound BDNF. Then, a TMB substrate solution is added to the wells and color develops in proportion to the amount of BDNF bound, the absorbance is measured at 450 nm (Synergy 2, BioTek).

##### Biochemical measurements in PBMCs

To carry out all biochemical determinations, PBMC samples will be first fractionated in cytosolic and nuclear extracts. For the preparation of cytosolic and nuclear extracts, it will be used a modified procedure based on the Schreiber et al. (68). PBMC pellets will be homogenized in 150 μL of lysis buffer consisting of 10 mmol/L HEPES at pH 7.9, with a cocktail of proteases and phosphatase inhibitors (Roche), 1 mmol/L EDTA, 5 mmol/L NaF, 1 mmol/L NaVO4, 0.5 mol/L sucrose and 10 mmol/L Na2MoO4. After 15 min the detergent Nonidet P-40 (Roche, Mannheim, Germany) will be added at a concentration of 1%. The tubes will be shaken for 30 s and the mixture will be centrifuged for 5 min at 8,000 g. The supernatant that constitutes the “cytosolic fraction” will be aspirated and the pellet will be resuspended in 50 μL of buffer supplemented with 20% glycerol and 0.4 M KCL. The mixture will be stirred for 30 min at 4°C, centrifuged for 5 min at 13.000 g and the supernatant, corresponding to the nuclear fraction, will be aspirated. Both fractions were stored at −80°C.

###### Protein Quantification

Once the nuclear extracts have been obtained, protein quantification will be carried out. The Bradford^©^ assay is one of the most popular methods to determine the concentration of a total protein in a sample. In this assay, proteins bind to Coomassie G-250 dye resulting in a color change from brown to bright blue and the formation of a protein-dye complex. The absorbance of the blue color produced is measured at 570–590 nm and is proportional to the protein concentration. Known bovine serum albumin concentrations with seven points between 0 and 0.8 mg/ml were used as the standard curve. For the measurements, the samples were diluted 1/20 and mixed with 10 μl of dilution or the standard with 200 μl of Bradford reagent and the absorbance was measured in the plate reader (Sinergy 2, BioTek, Germany).

*TrkB-FL and TrkB-T receptors:* Protein levels of receptors were quantified by Western blot analysis. In brief, 12.5 μg of cytosolic extracts were loaded onto electrophoresis gels. Protein samples were separated and transferred onto nitrocellulose membrane (Transfer Pack, Biorad) using a semi-dry transfer system and were blocked in 5% BSA for 1.5 h, and then the membranes were incubated overnight at 4°C with specific antibodies. Blots were imaged using an Odyssey® Fc System (Li-COR Biosciences) and quantified by densitometry (ImageJ®, NIH). We used β-actin as a loading control. All densitometry results are expressed as a percentage of the control. Given the counterbalancing effect of TrkB-T1 and TrkB-FL, we chose the ratio of TrkB-FL to TrkB-T expression (hereafter FL/T ratio) as our index variable for describing BDNF receptor expression.

### Exercise Intervention Program

Previous investigations by the exercise specialists who will lead this research have already performed the exercise protocol (69, 70). In short, the experimental group will receive supervised physical exercise treatment by high-intensity interval training (HIIT), alternating high and moderate intensities (20 min). Participants will exercise two non-consecutive days per week for 16 weeks under the supervision of a coach at the facilities provided by the University Hospital of Araba. All the exercises sessions will start and finish with blood pressure monitoring and training intensity will be controlled by HR monitoring (Polar M200, Kempele, Finland) and through the rate of perceived exertion using the Borg's original scale (6–20 point). Each session will include a 10 min warm-up with joint mobility and coordination exercises with continuous leg movement to facilitate the venous return and a 10 min cool-down period with basic core strengthening exercises and passive stretching exercises on the floor to ensure a progressive return to the resting values of both blood pressure and HR. The main portion of the training session will consist of 20 min of aerobic exercises on the bike developing progressively intensity. Intensity will be individually tailored to HR at moderate or vigorous intensities, adjusting the power and speed on the bike, to achieve the planned target HR (Table 1). The exercise specialists will keep detailed records of all the exercise sessions reporting the HR and Borg scale values of every interval. The importance of targeting moderate and high intensity will be emphasized.

**Table 1 T1:** Intervention program for the experimental group by High-intensity physical exercise program on the bike.

	**Protocol**			
	**High-intensity interval**		**Moderate intensity interval**	
**Weeks**	**Volume (min)**	**Intensity (% heart rate reserve)**	**Volume (min)**	**Intensity (% heart rate reserve)**
1–2	2	80	18	60
3–4	3	80	17	60
5–6	4	85	16	65
7–8	4:30	85	15:30	65
9–10	4:30	95	15:30	70
11–12	4:30	95	15:30	70
13–16	4:30	95	15:30	70

*Volume and intensity progression*.

Several strategies will be implemented to maximize adherence, including music in all sessions, individualized attention at the intervention sessions and telephone calls following missed sessions.

The protocol of HIT will carry out a 5–10-min warm-up period on the bike. After that participants will cycle for 30 s at high-intensity (i.e., HR values up to VT2 to peak intensity) followed by 60 s at moderate-intensity (i.e., HR values between VT1 and VT2). Four repetitions (1 rep = 30 s high-intensity followed by 60 s moderate-intensity) will be initially performed and gradually increased to nine repetitions will be completed. The training session will end with a 5–10 min cool-down period at moderate-intensity.

### Statistical Analysis

A general descriptive analysis of the sample will be performed to assess baseline homogeneity. The normality of quantitative variables will be assessed by the Kolmogorov-Smirnov test and results will be expressed as means and standard deviation or as median values and interquartile range in the case of non-normal distribution. Qualitative variables will be expressed as frequencies and percentages.

To respond to the main aim, analysis of covariance (ANCOVA) will be used to assess the improvement in functionality. The same test will be used to analyze the difference between the groups.

At baseline, an analysis of variance (ANOVA) will be performed to confirm that there is no difference between patient groups, but there is a difference with the control group.

Student's *t*-test for related samples will be used to assess changes after the physical exercise program between intervention patient groups, among normally distributed variables. Changes in the variables studied across the three visits will be assessed by an analysis of repeated measurements. The analysis of repeated measurements will be used to assess the evolution of the variables studied during the three visits. Non-normally distributed variables will be assessed using Wilcoxon test. Univariate and multivariate regression analysis will be performed to determine whether statistically significant differences are associated with the evolution of the functionality and clinical and cognitive symptoms. All statistical analyses were carried out using SPSS v23.0 and R v3.5.0 statistical software, with the significance level set at *p* < 0.05.

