Previous studies have shown that physical exercise is an effective antidepressant intervention (30), but no studies have been able to provide a comprehensive overview of the mechanisms that produce these benefits in terms of patient prognosis. This fact led us to conduct a longitudinal comparative study to assess the impact on FunctIonality and Neurocognition of an individualized moderate-to-vigorous physical EXercise Training in a population of patients with BD (FINEXT-BD study).

We hypothesize that this intervention will improve the functional status of patients and this improvement will be reflected in physical and biological parameters. Thus, the primary aim of this study will be to investigate whether the implementation of an individualized moderate-to-vigorous physical exercise intensity program as adjuvant therapy to standard drug therapy will improve the functional status of patients with BD, as compared to a group of patients with BD without intervention. The specific secondary objectives of the study will be to: (1) investigate whether the implementation of this exercise program modifies the cognition, the clinical symptoms and incidence of comorbidities; (2) investigate whether the implementation of this exercise program induces changes in the levels of oxidative and inflammatory parameters and these changes correlate with the evolution of clinical symptoms; (3) whether BDNF and TRkB-FL/TRkB-T ratio are associated with the evolution of the patient's functional and neurocognitive capacity, and (4) whether changes in the thickness of retinal layers as measured by OCT correlate with the functionality and neurocognitive function of BD patients.

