#### Randomization and Blinding

FINEXT-BD patients will be randomly assigned to the groups (1:1) using Random Allocation Software version 1.0.0 software. Study evaluators will be blinded to the treatment branch. Patients will continue their usual treatment and will be treated by their reference psychiatrist, who will be informed of patient's participation in the interventionist program and will make sure that the appropriate clinical treatment is administered.

The flow diagram of the study can be seen in Figure 1.

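### A related-samples t-test is assigned to a comparison between independent arms; it shows only within-arm change, and the plan does not clearly extend its ANCOVA to the secondary outcomes

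*Protocol article*

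**What the plan says.** All the tests are named in the Protocol article, section Statistical Analysis:

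- For the main aim, "analysis of covariance (ANCOVA) will be used to assess the improvement in functionality". The next sentence adds: "The same test will be used to analyze the difference between the groups".
- For change after the programme, Student's t-test "for related samples will be used to assess changes after the physical exercise program between intervention patient groups, among normally distributed variables".
- For the three visits, "Changes in the variables studied across the three visits will be assessed by an analysis of repeated measurements".
- For skewed data, "Non-normally distributed variables will be assessed using Wilcoxon test". The type of Wilcoxon test is not given.
- Earlier in the section, "The normality of quantitative variables will be assessed by the Kolmogorov-Smirnov test". That sentence goes on to say how results will be summarised (mean and SD, or median and interquartile range).

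The design is parallel-group. Under Randomization and Blinding, "FINEXT-BD patients will be randomly assigned to the groups (1:1"). The primary aim in the Introduction is whether exercise "will improve the functional status of patients with BD, as compared to a group of patients with BD without intervention".

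**The concern.** A related-samples test needs two measurements on the same person. The two patient arms are separate people, so the test named in the t-test sentence cannot make the comparison that the sentence describes. All it can deliver is a pre-post test inside one arm. The natural rank counterpart, the signed-rank test, has the same limit.

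This matters most for the secondary objectives: cognition, symptoms, oxidative and inflammatory markers, BDNF and retinal layers. Patients are assessed at three visits, and the cognitive battery includes the Stroop, TAVEC and Wisconsin tests. Practice effects, closer attention and the natural course of the illness could all move both arms in the same direction. A within-arm test credits that shared movement to exercise, whereas a between-arm test cancels it.

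**Working it through.** **1. The sentences side by side.**

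| Sentence concerns | Test named | What it can test |
|---|---|---|
| Main aim (functionality) | ANCOVA | Exercise versus TAU |
| Difference between the groups | ANCOVA | Exercise versus TAU |
| Change after the programme, between patient groups | Related-samples t | Change inside one arm |
| Non-normal variables | Wilcoxon, type not given | Inside one arm if signed-rank; between arms if rank-sum |
| Three visits | Repeated measurements | Depends on the model terms |

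Rows 2 and 3 give different tests for what reads as the same contrast, and nothing says which outcomes fall under which row. ANCOVA is introduced under the main aim. The related-samples sentence refers to variables in general.

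**2. What follows if benefit is read from the paired tests.** The plan states no figure to reproduce here, so this is an illustration.

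Inputs from the document: 40 per group and 10% losses (Sample Size), so 40 × 0.90 = 36 completers per arm; significance level 0.05 (Statistical Analysis), taken as two-sided.

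Assumptions not in the document: no treatment effect; both arms improve by the same amount *s*, in SDs of the raw score; pre-post correlation *r*; equal SD at both visits; normal data.

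The SD of change is √(2(1 − r)), so the standardised change is d = s / √(2(1 − r)). With s = 0.4 and r = 0.6:

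- d = 0.4 / √0.8 = 0.447
- non-centrality = 0.447 × √36 = 2.68, on 35 degrees of freedom
- probability that one arm's paired t-test is significant = 0.742
- the arms are independent, so P(exercise significant, TAU not) = 0.742 × (1 − 0.742) = 0.19

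Over a range of assumptions, each cell gives the probability that the exercise arm is significant, then the probability that exercise is significant and TAU is not:

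| | s = 0.3 | s = 0.4 | s = 0.5 |
|---|---|---|---|
| r = 0.5 | 0.42 / 0.24 | 0.65 / 0.23 | 0.83 / 0.14 |
| r = 0.6 | 0.50 / 0.25 | 0.74 / 0.19 | 0.90 / 0.09 |
| r = 0.7 | 0.62 / 0.24 | 0.85 / 0.12 | 0.96 / 0.03 |

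**3. Check by simulation.** 20,000 trials per setting, 36 per arm, no treatment effect, shared gain expressed in SDs of the change score:

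| Shared gain | Exercise arm significant | Exercise significant, TAU not | Between-arm t on change, significant |
|---|---|---|---|
| 0 | 2.5% | 2.4% | 5.0% |
| 0.2 | 21% | 16.8% | 5.3% |
| 0.3 | 42% | 24.6% | 5.2% |
| 0.4 | 65% | 22.9% | 4.7% |
| 0.5 | 83% | 13.8% | 4.8% |

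The first two result columns count significance in the direction of improvement only; the last is two-sided. The gains at r = 0.5 in step 2 are on this same scale, because √(2(1 − 0.5)) = 1, and the two sets agree. The between-arm test stays near 5% whatever the shared gain. The paired tests do not.

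**The case against.** The strongest reply is that the plan already has its between-arm test. The sentence on the difference between the groups follows the ANCOVA sentence and is not expressly limited to functionality. It can be read as giving ANCOVA to every arm comparison, with the paired t-test merely describing pre-post change and the word 'between' a slip. The repeated-measurements analysis may also carry arm and arm-by-visit terms, and an article can fairly leave those terms to the full protocol or analysis plan. On that reading nothing is lost, and the illustration describes a mistake the investigators would not make.

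Much of this stands. It limits the reach of the point and rules out several stronger readings that a reader might infer:

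- **That the randomised comparison is discarded.** Not supported: ANCOVA is named both for the main aim and for the group difference.
- **That FAST or GAF would leave ANCOVA if they failed the normality test.** No sentence says that Wilcoxon replaces ANCOVA. The Kolmogorov-Smirnov sentence itself governs how results are expressed, and the Wilcoxon sentence sits with the paired and repeated-measures analyses.
- **That the normality test makes the choice of method close to random.** Rejection rates depend on which variant is run, and the plan does not say. For data with skewness 1, simulated rejection is about 34% (n = 40) and 54% (n = 80) with the Lilliefors correction, but about 1% and 6% without it.
- **That Wilcoxon must be a within-arm test.** Signed-rank is the natural partner of a paired t-test, but a rank-sum test would compare arms.

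The reply does not rescue the sentence itself. As written, it gives a between-group question to a test that cannot answer it, and the reader must guess whether ANCOVA overrides it for the secondary outcomes.

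**Conclusion.** The point holds in a limited form. The mismatch between the related-samples test and the between-group question is an error on the face of the text and needs no assumption. The section also names ANCOVA for the group difference, so the fault is conflicting instructions for one contrast and an unclear scope for ANCOVA beyond functionality. It is not the absence of a valid test. The primary comparison on functionality is not shown to be affected.

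The harm is conditional on benefit in secondary outcomes being inferred from the paired tests. The 74% and 19% figures, and the 3–25% range, rest on an assumed shared gain and correlation that the document does not give. They are not error rates of the plan's stated main analysis.

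**What to change.** Rewrite the t-test and Wilcoxon sentences so that:

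1. Every exercise-versus-TAU contrast on a continuous outcome, primary or secondary, is estimated by ANCOVA adjusted for the baseline value of that outcome, or by a repeated-measures mixed model with arm, visit, arm-by-visit and baseline.
2. The between-arm method is fixed in advance and not selected by a normality pre-test. Skew is handled by transformation, by robust or bootstrap standard errors, or by rank-ANCOVA as a sensitivity analysis.
3. Paired t and Wilcoxon signed-rank results are labelled within-arm and descriptive, and are not used to claim an effect of exercise.

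The cost is wording in the protocol and analysis plan. Data collection, sample size and software are unchanged.
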